**Inclusion Criteria**
1.Histologically proven diagnosis of Kaposi’s Sarcoma (KS) fulfilling the clinical criteria for cART-refractory disease: defined as KS with clinical progression or stable disease after at least 3 continuous months of combined anti-retroviral, with virological and immunological response (defined at 4) 2.Available pre-treatment biopsy 3.Established on cART for at least 3 months without adverse events (AEs) associated with cART > grade 1 by National Cancer Institute (NCI) Common Terminology Criteria for Adverse Events (CTCAE) criteria version (v.) 5.0. Note: modifications of cART during screening are allowed provided patients meet all other eligibility criteria and are on effective new regimen for at least 2 weeks 4.HIV viral load < 200 viral copies/ml and CD4 + T-cell count ≥ 100 cells/µL at screening 5.Measurable disease by modified AIDS Clinical Trial Group (ATCG) Kaposi sarcoma response criteria 6.Eastern Cooperative Oncology Group (ECOG) performance status of ≤ 2 7.Be of ≥ 18 years of age 8.Adequate haematological and organ function, defined as follows: -Absolute neutrophil count > 1.5 × 10 ꝰ/L -Platelet count > 100.000/mcL, -Haemoglobin > 90 g/L, -Total bilirubin ≤ 1.5 × upper limit of normal (ULN) or ≤ 2xULN for patients with Gilbert’s syndrome or on HIV protease inhibitors, -Aspartate aminotransferase (AST)/alanine aminotransferase (ALT) ≤ 2.5 × ULN (up to 5 × ULN if liver metastases are present), -Serum creatinine ≤ 2.5 × ULN or creatinine clearance (CrCl) > 60 ml/min in subjects with serum creatinine ≤ 1.5 × ULN. Calculation of CrCl should follow institutional standards -International normalized ratio (INR) or prothrombin time (PT) ≤ 1.5 × ULN unless patient is receiving anticoagulant therapy as long as PT or partial thromboplastin (PTT) is within therapeutic range of intended use of anticoagulants. Activated partial thromboplastin time (aPTT) ≤ 1.5 × ULN unless patient is receiving anticoagulant therapy as long as PT or PTT is within therapeutic range of intended use of anticoagulants 9.Female participants must have a negative serum pregnancy test within 72 h prior to taking study treatment if of childbearing potential and agree use a highly effective method of contraception from screening through 120 days after the last dose of study treatment or is of non-childbearing potential 10.Participant must agree to not breastfeed during the study or for 90 days after the last dose of study treatment 11.Male participant agrees to use a highly effective method of contraception (see Sect. 4.4 for a list of acceptable birth control methods) starting with the first dose of study treatment through 120 days after the last dose of study treatment. Note: Abstinence is acceptable if this is the established and preferred contraception for the patient 12.Participant receiving corticosteroids may continue as long as their dose is stable for least 4 weeks prior to initiating protocol therapy 13.Participant must be able to understand the study procedures and agree to participate in the study by providing written informed consent

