### Translational investigational plan

The hypothesis that guides the translational biomarker plan associated with StarKap trial is centred on the role of effector tumour infiltrating T-cell as a mechanism underscoring disease-modulating activity from immunotherapy in KS. We hypothesise dostarlimab to elicit anti-tumoral response by reinvigorating the T-cells effector function within the tumour microenvironment. To this end, tumour, bloods and stools samples will be longitudinally collected.A) Tumour samplesTumour biopsy will be mandatory at screening. Optional tumour samples will be collected at cycle and at the end of treatment to characterise the phenotype and the transcriptional profile of the intra-tumoral immune infiltrate.The phenotype of the intra-tumoral immune system will be assessed by performing imaging mass cytometry using a pre-defined panel of 30 markers specific for both the innate and adaptive immune system. The relative expression of the markers of interest will be evaluated pairwise in pre-on treatment samples and analysed in relationship with response to treatment.Transcriptomic profiling will be conducted in parallel with imaging mass cytometry experiments on tumour samples. Patients with a partial response will be categorised as “responders,” while those with stable or progressive disease will be classified as “non-responders.” Pathway enrichment analysis and immune deconvolution analysis will be conducted comparatively between the two groups. The same comparisons will be performed between pre-treatment and on-treatment samples.Available evidence suggest that HHV-8 specific T cells response is pivotal to prevent KS development. To verify whether immunotherapy elicits anti-tumour response by inducing clonal T-cells expansion, we will perform targeted sequencing of the rearranged VDJ segments on the CDR3 region of the TCRBeta chain on DNA extracted from FFPE pre-treatment and on-treatment tumour samples.B) Bloods samplesExtra bloods samples will be collected at screening, cycle 4, cycle 8 and end of treatment.We will characterize baseline immune phenotype of PBMC and their changes during treatment using multi- parameter flow-cytometry. Mean and median values of the diverse immune cell populations detected by flow-cytometry will be measured and compared across timepoints, and between responders and non-responders.To investigate whether response to immunotherapy is associated with specific immune-response, we will perform targeted sequencing of the rearranged VDJ segments on the CDR3 region of the TCRBeta chain on DNA extracted T-cell receptor beta- chain (TCRB) repertoire in peripheral blood lymphocytes to assess for dynamic changes in clonality of the T- cell response.To assess whether response to anti PD-1 (defined as reported in the clinical objectives) is associated with a reduction in HHV-8 viral replication and increased immune response against HHV-8 we will evaluate the changes in HHV-8 DNA level by real-time PCR from whole blood samples at baseline, cycles 4, cycle 8 and at the EOT.To confirm determine if response to KS is associated with increase T-cells response against HHV-8, we will perform ex-vivo T-cells stimulation with a pool of overlapping peptides spanning selected HHV-8 reading frames (ORF) and assess the immune response using interferon gamma assay.C) Stools samplesThe functional interaction between commensal bacteria and host immune system has been widely recognized in humans and animal models [18]. HIV infection has been reported to alter the composition of the intra-mucosal T cells with consequent alteration of the intestinal barrier permeability and increased translocation of bacterial products into the blood stream [19]. Furthermore, the presence of alterations within the intestinal immune environment, has been reported to alter the composition of the gut microbiome in people living with HIV, and this has been associated with persistent chronic inflammation and peripheral T cells activation [20]. At the same time, the lack of microbiome diversity and the enrichment of specific taxa of commensal bacteria including Bifidobacteria, Akkermansia and Ruminococcaceae has been associated with reduced responsiveness to immunotherapy in patients with advanced malignancies through a direct effect of gut microbiome products on peripheral and intra-tumoral immune cells [21].To verify if the composition of the stool microbiome correlates with intra-tumoral and peripheral immune cells phenotype, and with response to dostarlimab, we will longitudinally characterize gut microbiome by sequencing hypervariable V1-V2 region of 16S rRNA gene from stool DNA collected at baseline.

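### Blood TCR clonality is the only readout named for a specific immune response, but it cannot tell tumour-associated clones from unrelated ones; add a tumour-matched clone measure beside it

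*Protocol article*

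**What the plan says.** All of this is in the Protocol article, mostly under Translational investigational plan.

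- **Aim of the blood TCR work** (blood samples): "To investigate whether response to immunotherapy is associated with specific immune-response".
- **Readout** (same sentence): TCR-beta sequencing of the "repertoire in peripheral blood lymphocytes to assess for dynamic changes in clonality". No sorted fraction, tracked clone or tumour-matched subset is named. Blood is drawn at screening, cycle 4, cycle 8 and end of treatment.
- **Tumour TCR work** (tumour samples): the same TCR-beta CDR3 region is sequenced on "DNA extracted from FFPE pre-treatment and on-treatment tumour samples".
- **Tumour availability**: the screening biopsy is mandatory, and entry requires an "Available pre-treatment biopsy" (Table 2, inclusion criterion 2). Later biopsies are not assured: "Optional tumour samples will be collected at cycle and at the end of treatment".
- **Background T-cell activity** (stool samples): altered gut microbiome in people living with HIV is linked to "persistent chronic inflammation and peripheral T cells activation".
- **Separate specificity assay** (blood samples): "ex-vivo T-cells stimulation with a pool of overlapping peptides spanning selected HHV-8 reading frames", read by interferon gamma. The article does not use it to identify clones in the TCR data.

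**The concern.** The question is about specificity; the measure is about evenness. A clonality index is computed from clone frequencies alone, so two repertoires with the same frequencies get the same value whatever their clones recognise. If tumour-associated clones expand in blood, the index may hardly move. If an unrelated clone expands, it may move clearly.

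The setting makes this more than theoretical. The article describes background peripheral T-cell activation in this population, and its Rationale section reports features of immune senescence in people with HIV and KS. With one arm and 20 patients, no control group shows how far clonality drifts without treatment.

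At stake is whether the blood TCR data can answer the question set for them. The article describes no link between blood clones and tumour clones, although both sequence sets are planned.

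**Working it through.** The plan states no figure here, so there is nothing to reproduce. The check asks how far clonality moves when the relevant clones expand and when an irrelevant one does.

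**From the document:** the readout (clonality of blood TCR-beta), the availability of pre-treatment tumour sequences, and the blood sampling times.

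**Assumed, because the article gives none of it:**
- The index: clonality = 1 - H / ln(n), where H = -sum of p ln(p) over the n clones observed.
- The background: 200,000 clones with power-law frequencies, exponent 0.6, 0.8 or 1.0.
- The depth: 100,000 sampled templates.
- Tumour-matched clones: 0.5%, 1% or 2% of blood in total, in equal clones.
- One unrelated clone at 2%.

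**Step 1. One scenario in full.** Exponent 0.8, tumour-matched share 1% spread over 200 clones.
- Each matched clone holds 1% / 200 = 0.005% of blood, or 5 templates in 100,000; after tripling, 15.
- The unrelated clone goes from 2,000 to 5,000 templates.
- Baseline clonality: 0.0957.
- Matched clones triple (1% to 3%): change +0.0009.
- Unrelated clone 2% to 5%: change +0.0175.

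**Step 2. All scenarios.**

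| Tumour-matched clones | Share before tripling | Change when they triple | Change when one unrelated clone goes 2% to 5% |
|---|---|---|---|
| 200 | 0.5% to 2% | about -0.004 to +0.008 | +0.012 to +0.020 |
| 1 or 5 | 0.5% or 1% | +0.002 to +0.012 | +0.012 to +0.020 |
| 5 | 2% | +0.011 to +0.021 | +0.013 to +0.020 |
| 1 | 2% | +0.016 to +0.027 | +0.012 to +0.020 |

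Compared scenario by scenario, the unrelated clone moves the index more in every case of the first two rows. In the third row the two are about equal. In the fourth the tumour clone moves it more.

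**Step 3. Sign.** With 200 matched clones tripling while the unrelated clone falls from 2% to 1%, clonality falls in eight of nine scenarios. The index can move against a true expansion of the relevant clones.

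**Step 4. A different assumed repertoire.** Take 50,000 clones, exponent 0.8 or 1.0, and 20 tumour-related clones expanding five-fold, with no sampling noise.
- Related share 0.05% to 0.5%: change -0.0005 to +0.0037. Doubling the top unrelated clone (2.5% to 8.8% of blood): +0.014 to +0.041.
- Related share 2%: change +0.011 to +0.023. Doubling the unrelated clone: +0.014 to +0.040, so comparable.

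**Reading.** Even where the tumour effect is the larger one, the two causes give changes of the same sign and similar size, so the index alone cannot tell them apart. A summed frequency of tumour-matched clones triples in Step 2 by construction. That is a statement of what it measures, not evidence of how well it would perform.

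**The case against.** **Condensed article.** The index definition, depth normalisation and any tumour-blood overlap analysis may sit in a full protocol or laboratory plan that is not shown. This stands for the details, and I make no finding of an undefined index. It does not remove the mismatch, because the article itself names clonality as the readout for a specific response.

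**Meaning of specific.** The word could mean an adaptive, clonal response in general, for which clonality is coherent. That reading is possible. Even so, the index would not show whether the clonal change concerns the tumour.

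**Specificity is assessed elsewhere.** A reader might infer that the trial has no measure of antigen specificity. That is not so: HHV-8 peptide stimulation with an interferon-gamma readout is planned, and the anti-HHV-8 T-cell response is an exploratory endpoint in Table 3. This stands and lowers the stakes. The assay covers selected reading frames only and is not linked to the TCR data.

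**Chronic activation is in each patient's baseline.** The readout is change over time, so stable activation cancels. This stands in part: what remains is fluctuation, which is noise, and the documents give no reason why it should differ by response.

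**The illustration depends on its inputs.** Spreading the tumour expansion over 200 clones and the unrelated one over a single clone favours the concern. This stands; the table shows the ordering changing when a 2% share sits in one to five clones.

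**Tumour matching is also a proxy.** Bystander T cells infiltrate tumours, and a baseline list misses clones that first appear on treatment. This stands, and is why the measure should be added beside clonality and not replace it.

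**Conclusion.** The concern holds in a limited form. The named readout cannot tell expansion of tumour-associated clones from unrelated expansions, so alone it does not answer the question set for it. Under the assumed repertoires, one unrelated clone going from 2% to 5% often moves clonality as much as or more than a tripling of tumour-matched clones, though not when those clones are few and already large. All sizes rest on assumed repertoire shapes, clone shares and depth; none comes from the article.

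Two stronger readings are tempting. One is that unrelated clones always dominate the index; the scenarios with few, large tumour clones contradict it. The other is that the blood results would be uninterpretable for the trial's guiding translational hypothesis. The documents do not support that: the hypothesis concerns effector T cells within the tumour and is addressed mainly by imaging mass cytometry, transcriptomics and TCR sequencing of tumour tissue. Blood clonality is one supporting readout.

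The importance is minor. The analysis is exploratory, and the primary safety and secondary efficacy results are unaffected.

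**What to change.** In Translational investigational plan, blood samples, pre-specify a second blood TCR measure alongside clonality:

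- For each patient, list the TCR-beta clonotypes found in the pre-treatment tumour sample.
- In each blood sample, sum the frequencies of those clonotypes.
- Describe the within-patient change from screening to cycle 4 and to cycle 8, and relate it to response.
- Compute this measure and clonality at a common sequencing depth.
- Report both descriptively, without a hypothesis test.

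The cost is bioinformatic work only. Both sequence sets are already planned, and no sample, visit or assay is added. Fixing the measure before the data are seen also avoids a later choice between indices.

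The limits should be stated with the results. FFPE samples with few T cells give short, noisy clone lists. Some tumour clones are bystanders, so matching narrows the readout without proving tumour or HHV-8 specificity. Clones that first appear on treatment will be missed, because this section makes later biopsies optional.

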
### Statistical analysis

With safety being elected as primary clinical endpoint for the study, no power calculation for hypothesis testing was required to formally power the study. Justification for a sample size of 20 subject was based on previous experience in the use of pembrolizumab in HIV-associated cancers [9, 22].

An interim analysis on adverse events will be conducted after the 6 th subject clears the 21-days safety window. Pending review of safety data by the trial steering committee in the first 6 subjects, in the absence of significant toxicity, the study will continue to the recruitment of the remaining 14 subjects without pause.

The final efficacy analysis on the whole will be conducted at the end of the study after the last patient has completed the treatment.

The safety population will include all subjects receiving at least one dose of dostarlimab. All participants who receive at least one dose of dostarlimab and undergo efficacy evaluation will be included in the efficacy population. No patients will be replaced as this would introduce bias; drop-out is likely to be informative in this population.

The primary outcome will be presented using descriptive measures of safety such as frequencies and percentages of adverse events grouped as categorical variables and means and standard deviations for normally distributed continuous variables.

Efficacy endpoints will be estimated descriptively by documenting ORR and progression free survival rates (PFSR) at 12-weekly timepoints. Progression free survival will be estimated using the Kaplan–Meier method from screening to progression or death. The PFSR estimates the proportion of participants who do not progress and are alive at 12 weeks timepoint.

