**Methods:**

The trial will enrol 20 patients in total. After completion of the screening procedures, participants will receive the first dose of dostarlimab within 28 days. Dostarlimab will be administered at the dose of 500 mg evry 3 weeks for the first 5 cycles, and at 1000 mg every 6 weeks thereafter. Treatment will continue until disease progression, unacceptable toxicity, or completion of 1 year of treatment. The first 6 patients will be enrolled in a safety-lead-in phase, if no dose-limiting toxicities (DLTs) will occur within the 21 days in the first 6 participants, trial will continue. Patients will be monitored for the emergence of adverse events until 90 days after the last dose of treatment. Tumour response will be assessed as objective response rate (ORR) at cycle 4, cycle 8 and end of treatment. Tissue, bloods, and stool samples will be collected at baseline, on treatment and at end of treatment to satisfy the related translation plan.

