So far, ICIs in HIV-associated KS have been tested in only one dedicated prospective trial. This is a phase Ib trial conducted in the US, which recently reported on the safety and efficacy of pembrolizumab (anti-PD1) in HIV-associated KS. The trial included patients with undetectable viral load and a CD4 count of at least 50 cells/µL. Among the 32 patients enrolled, 31% ad at least one immune-related AE (irAE) with 25% required systemic steroids. The ORR according to the ACTG criteria was 62.1%. The safety and the efficacy profiles did not differ according to the CD4 count [11]. Furthermore, no HIV-related complications, nor CD4 count alterations were reported during the study. This has been also confirmed in the other available studies testing ICI in PLWH for different oncological indications [12–14]. A cohort (N = 15) of patients affected by KS was also included in the AIDS Malignancy Consortium 095 Study, a multicentre phase I study, which tested nivolumab (anti-PD1) at 3 mg/kg every 2 weeks in PLWH with undetectable HIV-RNA and CD4 count of at least 100 cells/µL affected by solid tumours or KS. The incidence of adverse events of any causes in the whole cohort was 80%, and 25% of the participants experienced grade 3 or higher adverse events. Fatigue, nausea, diarrhea, rash, and lymphopenia were the most common AEs at least possibly related to nivolumab occurring in more than 10% of the subjects. All of which of grade 1 or 2. No significant changes in the HIV-RNA or CD4 count occurred in the study. The ORR per ACTG criteria in the KS subgroup was 40% [12].

No safety nor efficacy data are currently available for dostarlimab in PLWH. According to the latest product’s brochure, with a data cut-off in April 2024, overall, 2087 participants without HIV have been treated in clinical trials with dostarlimab either alone or in combination therapy. The safety profile of the monotherapy from the GARNET [15] phase III trial, enrolling 494 patients affected by advanced endometrial cancer progressing to platinum-based chemotherapy, reported an incidence of all causes adverse events in any patients, with nausea (53.9%), alopecia (53%) and fatigue (51.9%) being the most common. The incidence of grade 3 or higher adverse events was 70.5% in the dostarlimab arm. The most common immune-related (AE) were hypothyroidism (11.2%), skin rash (6.6%), arthralgia (5.8%), and alanine aminotransferase increase (5.8%) [15].

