**Secondary**	
A) To characterize the efficacy of dostarlimab in cART-refractory HIV associated Kaposi Sarcoma	1. Objective Response rate (ORR) evaluated at week 10 and week 31 (± 7 days) and end of treatment by modified AIDS Clinical Trial Group (ACTG) Kaposi sarcoma (KS) response criteria. For patients with visceral involvement Response Evaluation Criteria In Solid Tumours (RECIST) v1.1 will be used to complement modified ACTG response criteria 2. Progression free survival (PFS) from screening 3. Time to progression from the first evidence of documented objective response to dostarlimab

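### The efficacy population drops treated patients who are never evaluated, so the ORR (and PFS, if it uses the same set) could be overstated

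*Protocol article*

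**What the plan says.** The Statistical analysis section of the protocol article defines two analysis sets. For safety: "The safety population will include all subjects receiving at least one dose of dostarlimab". For efficacy: "All participants who receive at least one dose of dostarlimab and undergo efficacy evaluation will be included in the efficacy population". The second adds a post-baseline condition that the first does not have.

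The next sentence reads: "No patients will be replaced as this would introduce bias; drop-out is likely to be informative in this population".

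Table 3 lists the first secondary endpoint as "Objective Response rate (ORR) evaluated at week 10 and week 31 (± 7 days) and end of treatment". The abstract gives the same assessments by cycle (cycle 4, cycle 8 and end of treatment).

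For PFS, the Statistical analysis section says: "Progression free survival will be estimated using the Kaplan–Meier method from screening to progression or death". It adds: "The PFSR estimates the proportion of participants who do not progress and are alive at 12 weeks timepoint". It does not say which analysis set PFS uses.

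Nowhere does the article count unevaluated patients as non-responders or give another denominator for the ORR.

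**The concern.** A treated patient who dies or is lost before any efficacy evaluation has no recorded response. Counting that patient in the denominator lowers the ORR, and removing the patient raises it. The stated rule removes the patient.

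The rule also sits badly with the sentence that follows it. That sentence refuses replacement to avoid bias, on the ground that those who drop out probably differ from those who stay. If so, leaving the unevaluated out of the denominator lets in bias of the kind the sentence sets out to avoid.

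The ORR is the first-listed secondary endpoint, and the Conclusions name it among the things the trial will describe. With one arm of 20, readers will naturally set it beside the anti-PD-1 response rates in the Rationale (40% and 62.1%). A few patients more or fewer in the denominator can change that impression.

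**Working it through.** **No figure to reproduce.** The article states no target ORR, power or drop-out rate. The calculations below illustrate the size of the effect. The responder counts, the number unevaluated and the event times are assumptions.

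**ORR**

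- Treated patients: 20, the planned enrolment (abstract, Methods).
- Responders, r: 10 as the central assumption. The values 8 and 12 show the range and correspond to 40% and 60%, near the two rates cited in the Rationale.
- Treated patients with no evaluation at all, k: 0 to 4 (assumption).

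ORR as planned = r / (20 − k). ORR over all treated, with the unevaluated counted as non-responders = r / 20.

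| k | Denominator as planned | r = 8 | r = 10 | r = 12 |
|---|---|---|---|---|
| 0 | 20 | 40.0% | 50.0% | 60.0% |
| 1 | 19 | 42.1% | 52.6% | 63.2% |
| 2 | 18 | 44.4% | 55.6% | 66.7% |
| 3 | 17 | 47.1% | 58.8% | 70.6% |
| 4 | 16 | 50.0% | 62.5% | 75.0% |

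The all-treated figure stays in the k = 0 row whatever k is. For r = 10 the excess is 2.6, 5.6, 8.8 or 12.5 percentage points. Over the three values of r, one unevaluated patient adds 2.1 to 3.2 points and four add 10.0 to 15.0. With any responders at all, r / (20 − k) exceeds r / 20 once k is at least 1, so the direction is fixed.

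For scale, the exact 95% confidence interval for 10/20 is 27.2% to 72.8%.

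**PFS, if it uses the efficacy population**

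Assume 20 treated, k patients excluded at week 6 and 4 further events at week 10. The Kaplan–Meier estimate at week 12 is then:

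- Excluded patients left out: 1 − 4/(20 − k).
- Excluded patients kept in as deaths: (1 − k/20) × (1 − 4/(20 − k)).

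For k = 2 the first is 14/18 = 77.8%, and the second is 0.90 × 14/18 = 70.0%.

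| k deaths before any evaluation | Evaluated only | All treated |
|---|---|---|
| 1 | 78.9% | 75.0% |
| 2 | 77.8% | 70.0% |
| 3 | 76.5% | 65.0% |
| 4 | 75.0% | 60.0% |

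If the k patients are instead drop-outs censored at week 6, before the first event, they have left the risk set by week 10 in either analysis. For k = 2 the estimate is 14/18 = 77.8% with or without them. Only excluded deaths and undocumented progressions bias the Kaplan–Meier estimate; such drop-outs do not.

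**The case against.** The strongest reply is that few patients may be affected. The rule asks for an efficacy evaluation, not for attendance at week 10, and an end-of-treatment assessment is planned. A patient who stops early can be assessed then and stay in as a non-responder. If all 20 are evaluated, the two denominators are the same. Efficacy is also secondary and descriptive: no test, power target or decision rule uses the ORR, and the safety analysis already includes every treated patient. With one or two unevaluated, the shift is small beside the width of the interval for 20 patients.

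All of this stands, and it limits the size and weight of the point. It does not remove it, because a patient who dies or is lost with no evaluation of any kind is still excluded, and the resulting shift runs in one direction. A wide interval does not correct that.

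A reader might infer more than the article supports:

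- **That everyone who progresses or stops for toxicity before week 10 is lost.** Documenting progression is itself an evaluation, and the end-of-treatment assessment can bring early stoppers in.
- **That the bias grows at week 31 because progressors have left by then.** The article defines one efficacy population and does not say that it is cut again at each visit.
- **That PFS has a built-in event-free period of nine or ten weeks.** Entry does not require reaching week 10, and the PFS population is not stated.
- **That the cited 62.1% among 32 enrolled shows what such a rule does.** The article does not say how that trial formed its denominator or whether any patients left out had been treated.

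Whether the ORR should be a best overall response rather than a response at named times is a separate design question that does not follow from this rule.

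**Conclusion.** The concern holds for the ORR. The stated efficacy population omits treated patients with no evaluation, in a trial whose own plan expects drop-out to be informative, and nothing elsewhere in the article repairs this. Compared with an all-treated ORR that counts the unevaluated as non-responders, the planned ORR could be too high by 2.6 to 12.5 points for 1 to 4 such patients. This assumes 10 responders among 20 treated. The excess is zero if everyone is evaluated, and the actual number cannot be predicted from the article.

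For PFS the concern is conditional. If the efficacy population applies, excluding deaths before any evaluation conflicts with a definition in which death is an event. Under the event times assumed above, two such deaths move the 12-week estimate from 70.0% to 77.8%.

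This is a should-fix point, because efficacy is secondary and descriptive and no decision depends on it.

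**What to change.** - Define the efficacy population as all participants who receive at least one dose, identical to the safety population, and say that both ORR and PFS use it.
- Count any participant without a response assessment as a non-responder for the ORR, and report how many there are and why.
- Keep every death as a PFS event, whether or not an efficacy evaluation came before it.
- Report the ORR among evaluated participants as a labelled sensitivity analysis.

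The cost is wording only, with no extra patients, visits or data. The reported ORR may be slightly less favourable. The change also brings the efficacy population into line with the plan's own statement on informative drop-out.
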